### Sample size calculation

By means of MANOVA for repeated measurements within factors, the potential differences in effect of the five different stimulation modalities will be assessed. A minimal detectable effect size (f) of 0.15 on the main primary outcome parameter pain intensity (VAS) was chosen. The required minimum number of participating patients is negatively associated with the correlation between measurements during the cross-over. Unfortunately, no data of previous research on this correlation were available at the time of setting up this study. Therefore, we made an conservative guess and a correlation of 0.6 was chosen. Thus, assuming a power of 0.8 and a significance level (σ) of 0.05 , an a priori sample size of 48 is required.

### Randomisation and blinding

Randomization was performed with a computer based program at the beginning of the trial and no blocks were used since this is not viable in our study design. In our study design all patients in the crossover will be subjected to all five stimulation modalities in random order, resulting in 5! (120) different orders in which the stimulation modalities can be programmed. Only 48 (the required sample size) of these 120 potential different orders are selected at random by the computer to be used.

The specific order of the programming for an individual patient is revealed to the local SCS programmer only during each of the five crossover periods. The patient is blinded for the intervention by means of a mask that cannot be seen through. The outcome assessments at the end of each 2-week period are done by means of questionnaires. The statistician who performs the analysis of the measurements and questionnaires is blinded for the allocation key for the treatments for each patient.

### Statistical analysis

Data are analyzed using the latest version of IBM SPSS Statistics. Descriptive statistics are used to determine the frequencies of the demographic and secondary outcome parameters, and to describe measures of central tendency and of dispersion, dependent on the shape of their distribution. The Kolmogorov-Smirnov test is used to analyze whether or not the scores on the these parameters are normally distributed. The outcome parameters are analyzed using Mixed Linear Models for repeated measurements within factors model. These Mixed Linear Models model require normality of residuals. These models are however relatively robust against violations of this assumption [80]. Therefore, the results are presented as mean ± the standard deviation (SD). Furthermore, a Bonferroni test will be performed in the pairwise comparison of the modes of stimulation only if the result of the overall analysis results in the rejection of the H0-hypothesis of no significant differences between the modes of stimulation. Therefore, to test this H0-hypothesis we will use the traditional rejection zone of 5 %. The primary analysis will not make a distinction between primary implantation group vs. re-implantation group since the vast majority of the included patients will be SCS naïve. This matter should than be dealt with in a post hoc testing.

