### Aim

This study aims to compare the effects of five different SCS modalities in patients with CRPS and determine which frequency is most effective in terms of pain reduction; these frequencies are standard stimulation with 40 Hz , 500 Hz, 1200 Hz, burst and placebo stimulation.

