## Discussion

Data obtained from this trial will provide better insight as to whether SCS, as it is currently applied, is the best available therapy modality, or whether stimulation with a higher frequency or with burst stimulation results in better pain relief. Another result might be that these new modalities of stimulation are equally preferred by the patients. Irrespective of the outcomes, this trial will provide new insights into the mechanisms of action involved in SCS treatment and, particularly, in patients with CRPS.

For this trial, standard SCS was defined as stimulation with 40 Hz and corresponds with the normal stimulation setting used in our daily practice. The choice to select 500 Hz was based on studies reporting that blood flow and endogenous opioid release are at their maximum while applying SCS at this frequency [57, 59, 81]. The 1200 Hz stimulation was chosen because it is the maximum that can be generated with this IPG. Burst stimulation was selected because the stimulation differs significantly from tonic stimulation in terms of waveform and working mechanism. It is reported that burst SCS can effectively reduce pain in patients with neuropathic pain [17, 18, 82–84].

High-frequency SCS (HF-SCS) with 10,000 Hz is also available and multiple studies have shown its effect in pain patients and its ability to reduce pain over a longer period of time [85, 86]. Our 1.2 kHz stimulation does not approach the 10 kHz used in the latter studies, but no clinical studies are available that compare these frequencies. However, some animal studies have compared the effects of normal frequency SCS with different HF-SCS settings. Song et. al. compared conventional suprathreshold stimulation of 50 Hz with that of subthreshold HF-SCS at 500 Hz, 1 kHz and 10 kHz and concluded that the hypersensitivity after nerve lesions was reduced in all the HF-SCS groups and that the reduction was equal to that of the normal SCS group [87].

Burst stimulation is a new concept which requires a totally different programming algorithm in daily practice. The stimulation must be programmed to a sub-threshold current output level so that a patient will not experience paresthesia. This paresthesia free ‘side-effect’ can be used to incorporate a placebo element into the trial where paresthesia cannot be felt because the stimulation is switched off.

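### The 80% power applies only to the overall five-mode test; the gated Bonferroni step that answers the aim has no stated power and is stricter than it needs to be

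*Protocol article*

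**What the plan says.** The Aim section of the protocol article wants to "determine which frequency is most effective in terms of pain reduction", among 40 Hz, 500 Hz, 1200 Hz, burst and placebo.

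The Sample size calculation section names the test that it sizes: "By means of MANOVA for repeated measurements within factors, the potential differences in effect of the five different stimulation modalities will be assessed". Its inputs are "A minimal detectable effect size (f) of 0.15 on the main primary outcome parameter pain intensity (VAS) was chosen" and, for the correlation between periods, "we made an conservative guess and a correlation of 0.6 was chosen". Then, "assuming a power of 0.8 and a significance level" of 0.05, it concludes that "an a priori sample size of 48 is required". It gives no pairwise difference, no SD and no power for a pair.

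The Statistical analysis section fixes a two-stage rule. The overall hypothesis of no difference is tested at 5%, and "a Bonferroni test will be performed in the pairwise comparison of the modes of stimulation only if the result of the overall analysis" rejects it. The number of pairs is not stated.

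**The concern.** The overall test asks whether the five modes are all alike. It can reject only because placebo differs from the rest, and that would not show which active mode is best. The second stage has to show that, and the 80% does not carry over to it.

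The second stage also corrects twice. The overall test already guards the case in which all five modes are equal, yet Bonferroni then divides as if all 10 pairwise nulls could still be true. The stake is avoidable loss of power where the trial answers its own question, and a power figure that readers may attach to the wrong test.

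**Working it through.** **Inputs.** From the Sample size calculation: f = 0.15, correlation ρ = 0.6, alpha 0.05, power 0.80, N = 48. From the design: m = 5 modes, all received by every patient, so 5 × 4 / 2 = 10 pairs. Assumed here: all 10 pairs are tested (0.05/10 = 0.005 each, two-sided), compound symmetry, no dropout, and f defined on the within-mode SD.

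**1. The plan's own figure.** The noncentrality is λ = f²·N·m/(1 − ρ) = 0.0225 × 48 × 5 / 0.4 = 13.5. With the MANOVA degrees of freedom (4 and 44), power is 0.807 at N = 48 and 0.797 at N = 47. So 48 is reproduced, and it belongs to the overall test. The univariate repeated-measures F test gives 0.842 at N = 48.

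**2. From f to a pairwise difference.** f is the SD of the five means divided by the within-mode SD. It fixes a difference d only once a pattern of means is chosen. The standard error of a difference is √(2(1 − ρ)/N) = √(0.8/48) = 0.129 SD. Power at 0.005 for the largest difference is:

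| Pattern | SD of means | d (SD units) | d/SE | Power, paired t (47 df) | Power, pooled error (188 df) | N for 80% (pooled) |
|---|---|---|---|---|---|---|
| Two modes versus three | √(0.4 × 0.6)·d = 0.490d | 0.306 | 2.37 | 0.30 | 0.32 | 115 |
| One mode differs | √(0.2 × 0.8)·d = 0.400d | 0.375 | 2.91 | 0.49 | 0.53 | 77 |
| Evenly spaced | √0.125·d = 0.354d | 0.424 | 3.29 | 0.63 | 0.67 | 61 |
| Two extremes, three midway | √0.1·d = 0.316d | 0.474 | 3.67 | 0.76 | 0.80 | 49 |

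**3. How many nulls can remain.** If the five means are not all equal, the largest set of pairwise nulls that can hold together arises when four modes are equal: 4 × 3 / 2 = 6. A split of three and two leaves 3 + 1 = 4. The possible counts are therefore 6, 4, 3, 2, 1 and 0, and a first divisor of 6 (threshold 0.05/6 = 0.0083) is enough after the overall test. Bonferroni uses 10.

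**4. Comparing the rules.** Simulation with 40,000 trials per pattern, N = 48, ρ = 0.6, pooled error and a 5% overall F test first. The entries are power for the largest difference:

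| Pattern | Bonferroni | Holm | Shaffer, first divisor 6 | At least one true difference found (Bonferroni) |
|---|---|---|---|---|
| Two versus three | 0.325 | 0.353 | 0.389 | 0.743 |
| One differs | 0.529 | 0.552 | 0.590 | 0.811 |
| Evenly spaced | 0.669 | 0.680 | 0.716 | 0.779 |
| Two extremes | 0.783 | 0.786 | 0.809 | 0.812 |

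Holm gains 2.3 and 2.8 points in the one-differs and two-versus-three patterns, and 1.1 and 0.3 points in the evenly spaced and two-extremes patterns. Shaffer gains 2.6 to 6.4 points. Repeat simulations put its largest gain between 6 and 7 points.

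Power for one differing mode to be separated from all four others is 0.232 with Bonferroni, 0.275 with Holm and 0.296 with Shaffer.

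**5. Error control.** With four modes equal and the fifth far away, simulated familywise error was 0.025 (Bonferroni), 0.041 (Holm) and 0.041 (Shaffer). The highest value in any run was 0.043. When all five modes are equal, the overall test itself holds the error at 5%.

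**The case against.** The strongest reply is that nothing is stated wrongly. The sample size section ties 48 to the five-mode comparison and claims no power for pairs, and Bonferroni after an overall test controls familywise error. That stands: this is a possible improvement and not an error of validity.

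A reader might infer that the plan has about 50% power to find the best mode. The documents do not support that. They name no pattern of means, and 0.49–0.53 is the power for one given pair when one mode differs. Finding the best mode, read strictly as separating it from all four others, is a different quantity, at about 0.23 in that pattern. A reader might also expect many trials to reject overall and then find no pair. In simulation, at least one pair was significant in 88% to 97% of the trials that rejected overall, although one significant pair does not rank five modes.

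It is tempting to add that the plan would call modes equal after a non-significant test, since the Discussion says "Another result might be that these new modalities of stimulation are equally preferred by the patients". That sentence concerns patients' preference, which is recorded as a choice after the crossover, and not equality of mean VAS. Nor does the plan rule out intervals after a null result: only the Bonferroni test is conditional, and interval reporting is a detail that an article may leave out.

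Finally, Bonferroni has two real advantages. Its tests have simple matching simultaneous intervals, whereas a step-down rule may reject a pair with p = 0.007 whose Bonferroni interval (level 0.005) includes zero. Also, Shaffer's divisor of 6 relies on a well-calibrated overall test, while Bonferroni over 10 pairs does not. Both points stand as small costs of the change.

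**Conclusion.** The concern holds in a limited form. The 0.80 is correct for the overall test and says nothing about the pairwise step that serves the aim. At the same f and N, power for the largest pairwise difference lies between about 0.30 and 0.80 depending on the pattern of means. These figures rest on 10 pairs, compound symmetry, ρ = 0.6 and no dropout.

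The gated Bonferroni rule is valid but leaves some alpha unused. A step-down rule is never less powerful at the same N and alpha, but the gain is modest. When one mode differs, per-pair power rises from 0.53 to 0.55 (Holm) or 0.59 (Shaffer), whereas 80% would need about 77 patients under the present rule. It would be wrong to say that the change cures the shortfall. It is a cheap improvement worth making.

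**What to change.** In the Statistical analysis section, keep the overall 5% test, state that all 10 pairs are compared, and replace Bonferroni by one step-down rule chosen in advance:

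- **Shaffer:** order the 10 unadjusted p-values from smallest to largest. Compare the first five with 0.05/6, the sixth and seventh with 0.05/4, then use 0.05/3, 0.05/2 and 0.05. Stop at the first that fails.
- **Holm:** use divisors 10, 9, 8 and so on down to 1. This is the safer choice if the calibration of the overall test is in doubt.

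In the Sample size calculation section, add that 0.80 refers to the overall five-mode test. Giving the pairwise power by pattern, as in the first table above, would help but is optional.

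The cost is a few lines of wording and simple arithmetic on SPSS p-values, with no extra patients. The price is that step-down rejections lack simple matching simultaneous intervals. If Bonferroni intervals are reported beside them, say that the two may disagree. The change should be fixed while the statistician is still blinded to the allocation key.

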### Pre-trial assessment

Patients with an indication for neuromodulation are referred by their physicians to the SCS nurses for further evaluation, and to provide them with additional information about the procedure and lifestyle limitations. Also, a psychologist will screen the patient to rule out any psychological contraindication that might influence the outcome of the SCS trial. The patients are contacted by the researcher for trial information and enrollment once all the clinical inclusion criteria for SCS treatment have been met. After obtaining written obtained consent from the patient, the next phase in the trial can commence. It is noteworthy that patients who decline to participate in the trial will still be treated with regular SCS therapy.

### Baseline measurement T0

The patient is invited to our medical centre to participate in various test that are conducted as well as medical history and physical examination. All questionnaires must be filled in by the patient prior to this visit. Table 1 presents an overview of the tests and measurements that are performed during the entire course of this trial. The results of the T0 tests will serve as a baseline and all subsequent evaluations will be compared with these results. An additional requirement for the patients that still have an active SCS device is to switch off the stimulation for at least 1 week before T0. This will provide objective insight into the disease characteristics and pain that would otherwise be masked by the SCS therapy. Figure 1 presents a complete overview of the various phases in this trial.

### Trial stimulation and implantation

The trial stimulation is conducted at the various hospitals attended by the patients and lasts for 2 weeks. Only experienced physicians are allowed to perform implantation. During the test stimulation the patient is positioned in the prone position and spinal column landmarks are identified with fluoroscopy. Local anaesthetics are used during this procedure; however, a mild sedative or short-acting opioid can be used without compromising the patient’s ability to cooperate during the intra-operative testing. The surgical procedure used is left to the discretion of the physician in charge.

The cylindrical percutaneous Octrode™ lead (St. Jude Medical, Plano, TX, USA ) is primarily used in all patients to gain unilateral stimulation and is positioned under fluoroscopic guidance. The correct position is determined by means of intra-operative stimulation and is deemed successful if the induced paresthesia has an adequate overlap with the painful area. The lead is sutured to the fascia using an anchor. An extension cable is attached to the lead and is tunneled under the skin towards a suitable exit site. A temporary battery is attached to the external part of this extension cable during the trial period.

The parameters used for stimulation is up to the SCS nurse in charge, except for the mandatory frequency setting of 40 Hz. All other parameters (such as electrode configuration, pulse width and current output levels) are the result of the individual clinical paresthesia mapping. The trial period will generally last for 1 or 2 weeks and is considered successful if a patient has >50 % pain reduction on a VAS and/or has stated that the symptoms are much improved. All patients with a successful trial receive a permanent rechargeable internal pulse generator (IPG) from the Eon family line (St. Jude Medical, Plano, TX, USA) under general anaesthesia. The trial extension cable is removed and replaced with a new extension cable that is connected to the IPG. In some instances, a direct connection with the lead and IPG can be made if the length of the lead is sufficient. The pocket location for the IPG is free of choice and can either be in the lower abdomen or in the gluteal are. All materials are removed if a trial is unsuccessful and the patient is then excluded from further follow-up during this trial. The standard stimulation setting is further optimised during the regular checkups in the subsequent weeks. Antibiotic prophylaxis is given during both the trial and implantation in accordance with the local hospital antimicrobial guidelines.

### Follow-up measurement T1

Three months after the IPG implantation and therapy with normal tonic 40 Hz SCS, another assessment (T1) takes place. This serves as an evaluation of the effects of regular SCS on the previously described tests (Table 1). Enrollment into the crossover part of this trial can only commence after completion of this phase.

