### Follow-up measurement T2

The T2 assessment is performed when a patient has completed the 3-month period with the frequency of choice. This T2 evaluation enables us to compare all the primary and secondary outcomes parameters with the T1 assessment with standard SCS and the baseline T0 assessment prior to SCS therapy. The patient is actively asked whether they want to continue with the SCS program they have chosen, or want to switch to another one based on the crossover results.

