The question remains if a 2 week test period per frequency along with a 2 day wash-out to counteract the possible carryover effects of the various frequencies are enough. In clinical practice a patient can conclude whether the SCS is beneficial to him/her within a two week period during trial SCS. We choose to maintain the 2 week per period analogy in the crossover period which should provide the patient with enough time to decide if one of the test frequencies is beneficial or not. Moreover, by increasing the crossover period to 3 weeks or even longer the possibility of patient withdrawal from the study increases in case one of the test stimulations does not provide (sufficient) pain relief. This is further supported by what clinicians hear from patients that the pain returns when the stimulation is switched off. Some experience an instantaneous increase in pain while others report that it takes a few minutes or a few hours before the pain has fully returned, but never longer than 24 h. On these arguments we decided on a wash-out period of 2 days between the various stimulation modalities to be tested [88–90].

A potential pitfall in the design of the present trial that might influence the patient’s choice, is that the patients are preconditioned with standard stimulation for the first 3 months. On the other hand, if they do choose a SCS setting other than the standard one, it is a choice they make despite the odds being in favour of the standard stimulation.

Bias and in particular attrition bias is a serious problem that could affect the results of the trial. In our trial attrition bias will be handled by describing all patients that have dropped out of the trial before its completion and the reasons for dropping out/trial exit will be documented and provided in a flowchart in a separate manuscript with the results of this trial. The flowchart will adhere to the requirements of the CONSORT statement for transparent reporting of trials. Furthermore, data will be analysed using linear mixed models. Hence we can use all of the data, i.e., if a score is missing, it has no effect on other scores from that same patient.

With the results obtained from this study, that focuses solely on patients with CRPS, we aim to increase knowledge on the effects of SCS in this patient group. However, caution is advised when extrapolating these results to other neuropathic pain states because of the single-disease inclusion approach.

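### T0–T1 is presented as the effects of regular SCS, but it is an uncontrolled change in patients selected for having improved on 40 Hz

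*Protocol article*

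**What the plan says.** All places are in the Methods of the protocol article.

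- **Baseline measurement T0.** T0 precedes trial stimulation and is the reference for everything later: "The results of the T0 tests will serve as a baseline and all subsequent evaluations will be compared with these results".
- **Trial stimulation and implantation.** The screen's settings are left to the SCS nurse, "except for the mandatory frequency setting of 40 Hz". The screen is "considered successful if a patient has >50 % pain reduction on a VAS and/or has stated that the symptoms are much improved". For the others: "All materials are removed if a trial is unsuccessful and the patient is then excluded from further follow-up during this trial".
- **Follow-up measurement T1.** "Three months after the IPG implantation and therapy with normal tonic 40 Hz SCS, another assessment (T1) takes place". Its purpose is then stated without qualification: "This serves as an evaluation of the effects of regular SCS on the previously described tests".
- **Follow-up measurement T2.** T2 is meant to "compare all the primary and secondary outcomes parameters with the T1 assessment with standard SCS and the baseline T0 assessment".
- **Table 1.** The pain diary and the McGill questionnaire are taken at T0, T1, T2 and in the crossover. Questionnaires on mood, quality of life and function, sensory testing, strength, walking and activity monitoring are taken only at T0, T1 and T2. The table has no column for trial stimulation.

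**The concern.** Two features of the design stand between the T0–T1 change and the words used for it.

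The first is selection. The screen uses the same 40 Hz stimulation that T1 evaluates and admits patients because their pain fell or they felt much improved. Pain is also the main outcome. Patients who did not improve have no T1 value.

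The second is the missing control. Nobody goes unstimulated in parallel between T0 and T1, so natural course, placebo response and any change in other treatment are all part of the difference.

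What is at stake is the reading of the secondary results. If the stated purpose of T1 carries over into the results paper, a before–after change in screened patients will be reported as an effect. A patient or clinician deciding whether to start trial stimulation could take it as the benefit to expect. For the outcomes measured only at T0, T1 and T2, the trial has no controlled contrast to set against it.

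**Working it through.** **1. The plan's own figure.** The article gives no figure for the T0–T1 change. Its only related number is the sample size of 48 for the crossover. With f = 0.15, five measurements, correlation 0.6 and α = 0.05, the noncentrality at n = 48 is 0.15² × 5 × 48 / (1 − 0.6) = 13.5. With 4 and 44 degrees of freedom the power is 0.807, and 48 is the smallest n that reaches 0.80. The figure reproduces, and nothing below enters it.

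**2. Who contributes to T0–T1.** T0 is measured in everyone enrolled. T1 is measured only in those implanted, that is, in screen-passers. The observed difference therefore estimates the mean change given a pass.

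**3. Direction for pain.** Let R be relief at the screen, C the T0–T1 change that would be seen in all starters under stimulation, ρ their correlation, σ the SD of C and p the pass rate. If R and C are jointly normal and the screen cuts on R,

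E(C | pass) − E(C) = ρ × σ × φ(z)/p,

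where φ is the standard normal density and z the cut-off that passes a proportion p. The excess is positive whenever ρ > 0.

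The article gives neither ρ, σ nor p. With *assumed* ρ = 0.6 and σ = 2 VAS points:

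| assumed p | φ(z)/p | excess (points) |
|---|---|---|
| 0.9 | 0.1755/0.9 = 0.195 | 0.23 |
| 0.75 | 0.3178/0.75 = 0.424 | 0.51 |
| 0.5 | 0.3989/0.5 = 0.798 | 0.96 |

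**4. How far the size depends on assumptions.** A simulation applied the VAS criterion alone (more than 50 % reduction from T0). It assumed usual pain of mean 6 and SD 1.5, visit noise of SD 1.0–1.5 and a patient-level effect of SD 1.5.

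- True mean effect 1.5: passers showed a change of 3.3–3.7, with 18–26 % passing.
- True mean effect 2.5: passers showed a change of 3.8–4.2, with 34–41 % passing.

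The excess over the true mean effect is about 1.3–2.2 points. The direction agrees with step 3. The size differs severalfold because the inputs differ.

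**5. Per-starter illustration.** If explanted patients are counted as unchanged, the per-starter mean is p × D + (1 − p) × 0 = pD, where D is the mean change in passers. The ratio of D to that mean is 1/p:

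| assumed p | 0.9 | 0.8 | 0.7 | 0.6 | 0.5 |
|---|---|---|---|---|---|
| ratio | 1.11 | 1.25 | 1.43 | 1.67 | 2.0 |

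**6. Outcomes not used in the screen.** For thermography, sensory testing, strength, activity and similar tests, selection acts only through their correlation with relief at the screen. The article gives no such correlation, so the sign of the selection bias is open. The missing control applies to them regardless.

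**The case against.** The strongest reply is that the article never claims to estimate an effect in everyone who starts trial stimulation. Its aim is to compare five modalities, the sequence of screen, implantation and T1 is set out openly, and T1 can be read as describing implanted patients. The crossover includes a switched-off period meant to show the placebo share of relief, and 40 Hz against off is among the pairwise comparisons made if the overall test rejects. The Discussion promises a flowchart of dropouts with reasons.

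Much of this stands. All starters is a target population brought in here, and the modality comparison is not biased by this point. But the sentence on T1 speaks of effects and names no population. The switched-off period helps only for the measures repeated in the crossover, and only in screened patients. The Discussion covers preconditioning, attrition and single-disease scope, but not responder selection or the uncontrolled comparison.

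Some stronger readings are tempting and are not supported:

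- *The mixed model projects screen failures to improve like passers.* The Discussion says of the mixed-model analysis: "Hence we can use all of the data, i.e., if a score is missing, it has no effect on other scores from that same patient". A reader might infer that failures' T0 scores enter a T0–T1 model. No section says so, and the only contrast spelled out under Statistical analysis is between modes of stimulation.
- *Regression to the mean must inflate the change.* Eligibility appears to be settled before T0, and the article does not say which reading is the reference for the 50 % reduction. With a separate entry measurement and no true effect, the simulated mean change in all starters was 0.0. It was 0.27–0.55 only when T0 was itself the entry measurement.
- *Every outcome will look too favourable.* The argument on direction covers pain only.

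**Conclusion.** The point holds as a limited one on secondary reporting. T0–T1 and T0–T2 are uncontrolled changes in patients selected for relief or marked improvement on the same 40 Hz stimulation, and the article's wording gives them a causal meaning they cannot carry.

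For pain, the change will exceed the mean in all starters on one assumption: a positive correlation between relief at the screen and at T1. Its size cannot be derived from the document. The ratios of 1.11 to 2.0 rest on assumed pass rates and on the convention that failures are unchanged. The excesses in points rest wholly on assumed means, SDs and correlations and should not be quoted as estimates for this trial. For other outcomes no direction of selection bias is claimed, only that a before–after change without a control does not identify an effect.

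**What to change.** 1. Describe T0–T1 and T0–T2 as uncontrolled change among patients implanted after a successful 40 Hz trial stimulation, and drop the reference to effects of regular SCS.
2. Beside it, report how many patients started trial stimulation and how many failed it.
3. For VAS and the McGill questionnaire, add a supportive per-starter summary with failures counted as unchanged from T0, stated as a convention. It needs only T0 scores and pass/fail status. Use the VAS at the end of trial stimulation only if it was in fact recorded: Table 1 does not list it, and a pass could rest on the patient's statement alone.
4. Base placebo-corrected statements on 40 Hz pain relief on the randomised crossover contrast of 40 Hz with switched-off stimulation, noting that it too applies only to screened patients.

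The cost is a change of wording and a little extra reporting. The stated benefit of 40 Hz may become smaller. The screen, the crossover, the primary analysis and the sample size stay as they are.
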